## Background

The number of primary total knee replacement (TKR) procedures has grown by 73% in the past 10 years [1] and is projected to expand by more than 600% to 3.48 million procedures by 2030 [2]. Several facts are responsible for this increase in use, including (1) the prevalence of knee arthritis parallels the growing numbers of older adults, (2) increasing numbers of working aged adults are choosing TKR [1], and (3) TKR is a cost-effective intervention that reduces and eliminates pain. Despite these encouraging facts, significant variation remains in patient-reported functional improvement after TKR. An estimated 15-38% of patients report minimal functional improvement at 12 months, while another 10% report functional gains up to 3 times the national average [3,4]. Furthermore, our data suggests that the distribution of physical function at 12 months after TKR is bimodal [5]. The mechanism that underlies this varied functional improvement is not understood. While TKR researchers have identified some consistent predictors of poor gains in post-TKR function, no one patient attribute or surgical factor offers a satisfactory explanation for this outcome variation [6]. Importantly, poor emotional health as measured by the Mental Composite Score (MCS) of the SF36 is consistently associated with poor functional gain following TKR [3,4]. The NIH TKR Consensus Panel called for further research to address the role of patient attributes and rehabilitation regimens in functional outcome after TKR.

Exercise and activity improve global and knee-specific function in knee arthritis patients [7] and patient's confidence in their ability to manage their arthritis pain and function has been consistently associated with improved function, exercise, pain control, and self-care [8]. We have examined these associations in our pilot research and our data support a direct relationship between quantity of post-TKR exercise and activity and functional gain after TKR. This relationship was mediated by the patient's emotional health (SF36, MCS) and MCS was directly correlated with self-efficacy for arthritis self-care [9].

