### Recruitment, baseline assessment and randomization

The study coordinator recruits patients by reviewing a list of patients each week who are scheduled for upcoming TKR surgery, assessing patient's eligibility, calling patients to introduce the study and then mailing the consent form. The coordinator then follows up via telephone call. Patients complete and mail back a baseline assessment that includes the SF-36, the Pre-Surgery WOMAC, and a modified arthritis and exercise Self-Efficacy Scale. In addition, participants wear an ankle accelerometer (Step Activity Monitor) for four continuous days (at least one weekend day), and complete an exercise log.

Upon completing the baseline assessment, each patient is randomized into the Patient Self-Management Support intervention or to a usual care (control) condition. The study uses a stratified simple random sampling (S-SRS) of TKR patients to assure that participants represent subgroups of patients who may respond differently to the intervention. Patients are stratified by gender (two categories), BMI (three categories, < 30, 30-35, and > 35), and emotional health (SF36/Mental Composite Score; MCS) (three categories, < 45, 46-60, and > 60). This sampling scheme ensures that the sample includes wide variation in pre-operative BMI and MCS and gender balance. The categories are based on the distribution of pre-operative measures in a national sample. There are 2 × 3 × 3 = 18 strata in total. Within each stratum, 5 patients are randomized to intervention group and 5 to control group. The order of the two blocks is randomly permuted. Total target enrollment for the trial is 180 patients.

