#### Sample size considerations and statistical analyses

##### Sample size estimation

Sample sizes were calculated using the method developed by Frison and Pocock [37] with the SF-36 PCS as the primary outcome. Because patients are randomized within surgeon, we assume complete randomization of the study subjects to each treatment arm. We used the mean changes of repeated measures to estimate the required sample sizes based on Analysis of Covariance (ANCOVA) method. The mean change is defined as the difference between each subject's mean post-treatment PCS (the mean of 6 and 12 month PCS) and the baseline measurement.

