##### Analysis Plan

We will test the self-care support program's effect, both overall and in the latent low and high function response groups, as predicted by baseline characteristics on post-TKR 6 and 12 month functional outcome. We will apply mixture models with two latent classes (or GLLAMM), where the post-operative change in global function (PCS/SF36) at 6 or12 months is the primary outcome. The main predictors of the model include intervention indicator (0 = control versus 1 = intervention), data collection time points, and the interaction term between intervention indicator and time points. The treatment effects will be evaluated by testing the significance of the coefficient of intervention indicator and an interaction term of time and the intervention indicator. In the analysis, we will adjust for other patient characteristics that may moderate the intervention effect or reduce unexplained variability including gender, age, baseline function score, BMI, depression, anxiety, or social support. Potential moderating effects of each variable on the intervention will be examined by including interaction terms with the intervention indicator. The intervention effects on changes in knee pain, function using WOMAC sub-scores, number of daily repetitions and mean steps/hour on step activity monitor, and self-efficacy scores) will be analyzed using similar approaches. If the proposed intervention is effective, the post-TKR increases in home exercise and activity levels, and self-efficacy score in the intervention condition should be significantly greater than in the control condition. Next, we will examine whether the improvement in Stanford Arthritis Self-Efficacy scores predicts increases in home exercise and activity levels. Using a similar approach, we will test whether higher levels of home exercise (number of daily repetitions) and physical activity (mean steps/day on accelerometer) at 8 weeks post-TKR are associated with greater improvement in 6 and 12 month post-TKR global physical function and knee function.

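### Emotional health (MCS) is the only randomisation stratum not named among the model's covariates and moderators; separately, the sentence on randomising within surgeon does not match the allocation scheme

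*Protocol article*

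**What the plan says.** **Allocation** (Protocol article, Recruitment, baseline assessment and randomization). "Patients are stratified by gender (two categories), BMI (three categories, < 30, 30-35, and > 35), and emotional health (SF36/Mental Composite Score; MCS", the last also in three categories, giving 2 × 3 × 3 = 18 strata. The stated purpose is to represent subgroups whose response to the intervention may differ. "Within each stratum, 5 patients are randomized to intervention group and 5 to control group", and "Total target enrollment for the trial is 180 patients". Surgeon is not a stratification factor.

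**Prognosis** (Background). The article states that "poor emotional health as measured by the Mental Composite Score (MCS) of the SF36 is consistently associated with poor functional gain following TKR".

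**Model** (Analysis Plan). The model adjusts for patient characteristics that may moderate the effect or reduce unexplained variability, "including gender, age, baseline function score, BMI, depression, anxiety, or social support". Each is also to be tested as a moderator through an interaction with arm. The Potential moderators section names gender, BMI, depressive symptoms, trait anxiety and social support among others, in addition to the measures described before it. It does not name MCS either.

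**Sample size** (Sample size estimation). "Because patients are randomized within surgeon", the section goes on to assume complete randomisation to each arm.

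**The concern.** A trial is normally analysed by the factors it was randomised by. Stratification makes the arms more alike on MCS than chance would, so the true variance of the treatment difference falls. A model without MCS does not see that reduction: its standard error is too large, its test is conservative and some power is lost. The article gives its own reasons to expect MCS to matter, both as a predictor of functional gain and as a factor by which response may differ. Yet MCS is the one stratifier of three that the list does not name, so no arm-by-MCS test is explicitly promised.

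The second issue is one of description. Allocation within surgeon, complete randomisation, and a 5:5 scheme in 18 gender × BMI × MCS strata are not the same design. A reader cannot tell from the article whether surgeon was balanced by design.

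**Working it through.** **Inputs from the article (Effect Size).** Difference 4 PCS points; SD 10.9; correlation 0.65 between the two post-treatment measures and 0.50 between pre- and post-treatment; one baseline and two post-treatment measures; 75 completers per arm; two-sided alpha 0.05.

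**Input that is an assumption.** R², the share of residual PCS variance that MCS explains beyond the other covariates. The article gives no MCS–PCS correlation. I show 0 to 20%, with 5% to 10% as the working range.

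**Step 1: reproduce the stated power.** The ANCOVA variance factor for the mean of two post-treatment measures is (1 + 0.65)/2 − 0.50² = 0.825 − 0.25 = 0.575.

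- Effective SD = 10.9 × √0.575 = 8.265.
- SE₀ = 8.265 × √(2/75) = 1.350.
- Two-sided power = Φ(4/1.350 − 1.96) = 0.842 (stated: above 0.83).
- One-sided power = Φ(4/1.350 − 1.645) = 0.906 (stated: 0.90).

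Both figures reproduce, and no surgeon or stratum term enters. Allowing for 15% loss, 75/0.85 rounds up to 89 per arm, in line with 180/2 = 90.

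**Step 2: include MCS.** SE₁ = SE₀ × √(1 − R²); power = Φ(4/SE₁ − 1.96).

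**Step 3: leave MCS out although allocation balances it.** The true SE is SE₁ but the model reports SE₀.

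- True alpha = 2 × [1 − Φ(1.96/√(1 − R²))].
- Power = Φ((4 − 1.96 × SE₀)/SE₁).

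| R² (assumed) | SE₁ | True alpha, MCS out | Power, MCS out | Power, MCS in | Gain (points) |
|---|---|---|---|---|---|
| 0 | 1.350 | 0.050 | 0.842 | 0.842 | 0 |
| 5% | 1.316 | 0.044 | 0.848 | 0.860 | 1.2 |
| 10% | 1.280 | 0.039 | 0.855 | 0.878 | 2.3 |
| 20% | 1.207 | 0.028 | 0.869 | 0.912 | 4.3 |

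The like-for-like gain is the difference between the two power columns in the same row. The figure 0.842 is the comparator only when MCS explains nothing.

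**Limits of the calculation.** It follows the ANCOVA used for the sample size, not the two-class mixture model planned for the analysis. It takes MCS as fully balanced among completers. SE₀ allows for baseline PCS only; if depression, anxiety or other covariates also explain variance, both power columns rise and the R² left to MCS shrinks.

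**Step 4: the surgeon sentence.** Patients are allocated individually in both descriptions, and Step 1 contains no surgeon term. Removing the within-surgeon premise leaves the calculated power at 0.842 and N at 180.

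**The case against.** The strongest defence is that MCS is not excluded. The covariate list is introduced as a set of examples, and MCS meets its stated criterion. The Potential moderators section adds to measures already described, which include the SF-36. The latent response groups are to be predicted from baseline characteristics, and MCS could be one of them. Depression and anxiety are named and carry much of the same information, so what MCS adds could be close to nothing. The final covariate list is also commonly settled in an analysis plan that is not shown.

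Most of this stands, and it limits the point. A reader might infer that MCS is left out of the model, or that its moderating effect will not be tested; the text supports only that MCS is not named. Nor is the closing alternative in the list a fault in itself, since fixing the exact set can be left to the analysis plan. What remains is that the article does commit to a list, names two of its three stratifiers and passes over the one its Background stresses. Depression and anxiety are separate scales and only partial proxies for the MCS stratum.

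On surgeon, the sentence can be read loosely as saying that patients, not surgeons, are the randomised units, so that each surgeon has patients in both arms. That fits a single centre with individual allocation. It still does not describe the stratified scheme given earlier in the article.

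**Conclusion.** The point holds as a modest, avoidable loss of efficiency together with an inconsistent description of allocation. With R² of 5% to 10%, omitting MCS costs about 1.2 to 2.3 points of power and gives a true alpha of 0.044 to 0.039. With R² near zero it costs nothing. The error is conservative: type I error is not inflated, and on these assumptions power stays above the stated 0.83 either way.

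Two stronger inferences are not supported. One is that the sample size depends on randomisation within surgeon: the stated power reproduces without any surgeon term, so this is a wording conflict and not a sample-size error. The other is that the surgeon phrase must be deleted and a surgeon effect fitted. Deletion presumes which section is right, and a surgeon term is a modelling preference, because the article gives neither the number of surgeons nor an intraclass correlation.

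**What to change.** 1. In the Analysis Plan, name baseline MCS (as the stratum category or continuous) with baseline PCS, gender and BMI as covariates in the primary model.
2. Add the arm × MCS interaction to the moderator tests.
3. Reconcile the within-surgeon and complete-randomisation wording in Sample size estimation with the 18-stratum 5:5 scheme in the Recruitment, baseline assessment and randomization section. The sponsor should confirm which describes the allocation actually used and state surgeon's role, if any.

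The cost is wording. MCS comes from the baseline SF-36 that patients already complete. As a three-level category it uses 3 − 1 = 2 degrees of freedom, and its interaction with arm 2 more in the moderator test; as a continuous score, 1 and 1. That is small against 2 × 75 = 150 completers. N need not change.

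### The 8-week exercise and steps analysis names no adjustment for pre-surgery activity, although baseline accelerometer data are collected

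*Protocol article*

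**What the plan says.** All analysis statements below are in the Analysis Plan section of the protocol article.

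- **8-week analysis.** After the comparisons between arms, the section states: "we will test whether higher levels of home exercise (number of daily repetitions) and physical activity (mean steps/day on accelerometer) at 8 weeks post-TKR". The outcome in this test is the later gain in global and knee function, at 6 and 12 months. The section introduces the test as a similar approach to what precedes it.
- **Covariates.** The section has one adjustment list, written for the PCS model and introduced as open-ended: "gender, age, baseline function score, BMI, depression, anxiety, or social support". No activity or exercise measure is on it.
- **Comparisons between arms.** These concern changes from baseline: "The intervention effects on changes in knee pain, function using WOMAC sub-scores" and, in the same sentence, "number of daily repetitions and mean steps/hour on step activity monitor, and self-efficacy scores) will be analyzed using similar approaches". No separate covariate list is given for them.
- **Baseline data.** The section on recruitment, baseline assessment and randomization describes "a baseline assessment that includes the SF-36, the Pre-Surgery WOMAC, and a modified arthritis and exercise Self-Efficacy Scale". It adds that "participants wear an ankle accelerometer (Step Activity Monitor) for four continuous days (at least one weekend day), and complete an exercise log".
- **Log timing.** The Exercise and Activity section, under Mediators, places completion of the log at 8 weeks and 6 months and does not mention baseline.

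**The concern.** The 8-week analysis compares patients by how much they walk and exercise after surgery. Nobody is randomised to that. A patient who was active before surgery and remains active at 8 weeks enters the analysis as a high-exposure patient, whatever the post-operative period contributed. If prior activity also bears on functional improvement, the estimated association mixes the two.

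This matters because the Study Design section makes the roles of home exercise and physical activity in functional improvement a study aim. The Background hypothesis also runs through adherence to exercise and activity. An association that partly describes who was active beforehand is weak support for that chain. The variable needed to separate the two, at least for steps, is already measured.

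A smaller uncertainty concerns the randomised comparisons of WOMAC pain, steps, repetitions and self-efficacy. The only outcome-type baseline named is a function score. That is the own baseline of PCS and, arguably, of WOMAC function, but not of these other outcomes.

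**Working it through.** **1. Level or change.** The sentence just before the 8-week analysis relates improvement in self-efficacy to increases in exercise and activity. The 8-week sentence speaks of levels at one time point. The text thus uses both ideas, and here the exposure is a level, so pre-surgery activity is not removed by subtraction.

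**2. What the coefficient estimates.** Let A0 be pre-surgery activity, A8 activity at 8 weeks, Y functional improvement and C the named covariates. Suppose Y depends on A8 with coefficient b8 and on A0 with coefficient b0, given C. Let d be the slope of A0 on A8, given C. Leaving A0 out, the coefficient of A8 estimates

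b8 + b0 × d.

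The extra term b0 × d vanishes only if prior activity is unrelated to improvement given C (b0 = 0), or unrelated to 8-week activity given C (d = 0). Since habits persist, d is plausibly positive. The sign of b0 is open: previously active patients may recover better, or may have less room to improve. Baseline function and BMI are on the list and would absorb part of this, but neither is a measure of activity. The document gives no value for b0 or d, so no size can be attached.

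**3. Whether the data exist.** Steps: yes, from four days of accelerometer wear before surgery. Repetitions: unclear. One section has the log completed at baseline; another lists only 8 weeks and 6 months.

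**4. Companion point: the plan's own figure first.** The only power figure with full inputs is for PCS: SD 10.9, correlation 0.65 between post-treatment measures and 0.50 pre to post, 4-point difference, 75 completers per arm, ANCOVA on the mean of two follow-ups.

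- Variance factor: (1 + 0.65)/2 − 0.50² = 0.575
- SD: 10.9 × √0.575 = 8.27; SE: 8.27 × √(2/75) = 1.350
- Power: 0.842 two-sided and 0.906 one-sided, against the stated values of above 0.83 and 0.90

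The figure reproduces. Baseline adjustment is therefore part of the authors' method for PCS, and nothing is lost there.

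**5. Size if own baselines were left out.** The document gives no correlation for WOMAC pain, steps, repetitions or self-efficacy, so the pre-post correlation r is assumed. With one follow-up and equal SDs, the variance is proportional to 2(1 − r) for a change score and to 1 − r² with the own baseline as covariate. The SE ratio is √(2/(1 + r)).

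The last column adds baseline function as a covariate. It assumes that baseline function correlates 0.5 with the own baseline and predicts follow-up only through it. The change-score variance is then 2(1 − r) − 0.25(1 − r)², and the comparator stays at 1 − r².

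| r (assumed) | Change score | Own-baseline ANCOVA | SE ratio | SE ratio with baseline function |
|---|---|---|---|---|
| 0.3 | 1.40 | 0.91 | 1.24 | √(1.2775/0.91) = 1.18 |
| 0.5 | 1.00 | 0.75 | 1.15 | √(0.9375/0.75) = 1.12 |
| 0.7 | 0.60 | 0.51 | 1.08 | √(0.5775/0.51) = 1.06 |

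**The case against.** The strongest reply is that this is a condensed article. The covariate list is open-ended, the 8-week sentence refers back to a similar approach, and a full plan may well add baseline activity. The article also claims only association. This has force: the document does not rule the adjustment out. It does, however, fix the exposure as a level and name seven covariates, none of them activity, for a question that it makes a study aim. Asking for the one most obvious confounder to be named is fair.

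A reader might infer four stronger things that the document does not support.

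- *Own baselines are omitted from the randomised comparisons.* The text says only that the approaches are similar. In the PCS model the baseline function score is naturally read as that outcome's own baseline, so a similar approach for steps or self-efficacy may mean substituting theirs.
- *Those comparisons fail to separate pre-surgery activity.* They analyse changes, so the baseline is already subtracted, and under randomisation they are unbiased in expectation. Only precision is in question.
- *The 8-week analysis overstates the benefit of exercise.* The sign of b0 is unknown, so the bias could run either way.
- *The primary comparison loses power.* The PCS model names baseline function and its stated power reproduces, so a calculation for PCS without that covariate does not describe this plan.

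**Conclusion.** The point holds for the 8-week analysis. As written, it is a non-randomised comparison of activity levels with no named adjustment for pre-surgery activity, so its result can partly reflect activity before surgery. This rests on two assumptions: that prior activity carries over to 8 weeks, and that it relates to functional improvement beyond the named covariates. Size and direction cannot be determined from the document. Adjustment would remove this one source of confounding; it would not make the association causal.

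The own-baseline question is a minor clarification. If own baselines were left out, the cost would be an SE about 24%, 15% or 8% larger at assumed correlations of 0.3, 0.5 or 0.7. This falls to about 18%, 12% or 6% under the illustrative assumption about baseline function. The primary PCS comparison is unaffected.

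**What to change.** 1. In the analysis of 8-week exercise and activity against 6- and 12-month function, name baseline accelerometer steps as a covariate. The data are collected, so the cost is one term in the model and one line of text.
2. Reconcile the two statements on when the exercise log is completed. If comparable repetitions are recorded before surgery, add them to the same model. If not, say so and state the limitation for the repetitions result. Until this is settled, it cannot be said that this adjustment needs no new data.
3. State that similar approaches, for WOMAC pain, steps, repetitions and self-efficacy, means including each outcome's own pre-surgery value as a covariate. For WOMAC, steps and self-efficacy this needs no new data; repetitions depend on item 2.
4. While editing, use one unit for the step measure. The Analysis Plan gives steps per hour in one sentence and steps per day in another, and the baseline covariate should match the follow-up measure.

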Based on the existing evidence, we hypothesize that a Patient Self-Management Support intervention that targets self-efficacy for physical activity and independent activity and exercise during the peri-operative TKR period will improve actual adherence to independent exercise and activity and, thus, maximize 6 and 12 month functional outcomes among post- TKR patients. This paper describes an ongoing study that is testing this hypothesis.

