## Methods/Design

### Study Design

This prospective randomized clinical trial (RCT), funded by the National Institute for Arthritis and Musculoskeletal and Skin Diseases; NIAMS), is testing the efficacy of a theory-based telephone-delivered patient self-management support intervention to optimize post-TKR patient functional outcomes. The study participants are randomized to the Patient Self-Management Support intervention or to a usual care (control) condition, defined as care as prescribed by the patient's orthopedic surgeon or health care provider. The study seeks to assess the effect of the intervention on post TKR functional improvement, and understand the mechanisms of intervention effect by evaluating the roles of home exercise, physical activity, exercise self-efficacy, and participant attributes on functional improvement after TKR. It is hypothesized that, as compared to the control condition, patients receiving the Patient Self-Management Support intervention will have significantly greater increase in 6 and 12 month global (SF36/PCS) and knee-specific (WOMAC-Western Ontario and McMaster Universities Osteoarthritis Index) function. We also hypothesize that the intervention will enhance self-efficacy for exercise and that, in turn, increased self-efficacy will be associated with higher levels of home exercise and physical activity at 8 weeks and 6 and 12 month post-TKR. The study has approval from the Institutional Review Board of the Office of Human Subjects at the University of Massachusetts Medical School.

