##### Exercise and Activity

A *Step Activity Monitor *(accelerometer) assesses mean steps per day and activity intensity (steps per minute). The monitor provides a summary of total number of steps/cycle per 24 hour period and percent time/day that the individual is active at high/moderate/low activity, % of day inactive, and maximum sustained intensity for 5 and 30 minutes [31]. In addition, participants complete an *exercise (paper) log *to record the number of daily exercise sessions, repetitions and sets for each of the core home-based physical therapy exercises. The log is completed at 8 weeks and 6 months.

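### The mechanism aim is analysed as separate associations that can all be significant without any mediation, and the step measure changes name between two of them

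*Protocol article*

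**What the plan says.** The protocol article states a mechanism aim. Under Study Design the trial seeks to "understand the mechanisms of intervention effect by evaluating the roles of home exercise, physical activity, exercise self-efficacy, and participant attributes on functional improvement" after surgery. The Background gives the full chain: targeting self-efficacy and exercise "will improve actual adherence to independent exercise and activity and, thus, maximize 6 and 12 month functional outcomes among post- TKR patients". Self-efficacy and exercise/activity then stand under the heading Mediators.

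The Analysis Plan describes three analyses:

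1. Arm to mediator: intervention effects on "number of daily repetitions and mean steps/hour on step activity monitor", and on self-efficacy scores.
2. Self-efficacy to activity: "we will examine whether the improvement in Stanford Arthritis Self-Efficacy scores predicts increases in home exercise and activity levels".
3. Activity to function: whether 8-week daily repetitions and "physical activity (mean steps/day on accelerometer") are associated with improvement in 6- and 12-month global and knee function.

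The third is said to follow a similar approach to the second. Neither description says whether arm is in the model. No quantity that joins the links is described. On the device, the Exercise and Activity section says that it "assesses mean steps per day and activity intensity (steps per minute"); steps per hour is not among its listed outputs.

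**The concern.** Randomisation protects the comparison of arms on each mediator. It does not protect the association between 8-week activity and later function, which is observational even inside a randomised trial. Patients who recover quickly may walk more at 8 weeks and also score better at 6 and 12 months, whether or not walking contributed. A significant arm-to-steps link and a significant steps-to-function link are then both expected, although none of the treatment effect runs through steps. Three separate tests cannot tell this situation from true mediation, and they give no size for the mediated part.

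The step measure raises a second, smaller matter. The arm effect is to be tested on steps/hour and the link to function on steps/day. Either this is a slip of units or the two links concern different variables, and the text does not settle which.

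**Working it through.** **The plan's own figure.** The Effect Size section gives SD 10.9, post-post correlation 0.65, pre-post correlation 0.50, 75 completers per arm and a 4-point difference. For ANCOVA on the mean of two post measures, the effective SD is 10.9 × √((1 + 0.65)/2 − 0.50²) = 8.265. Power is 0.842 two-sided (stated: above 0.83) and 0.906 one-sided (stated: 0.90). The figure reproduces, but it concerns the total effect. No figure is stated for mediation.

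**What significant links imply about size.** With 150 completers:
- SE of arm to steps = √(4/150) = 0.163 SD, significant from 1.96 × 0.163 = 0.32 SD.
- SE of steps to mean PCS ≈ 8.265/√150 = 0.675 points per SD, significant from 1.96 × 0.675 = 1.32 points per SD.
- Product of the two thresholds = 0.32 × 1.32 = 0.42 points, or 0.42/4 = 11% of the target.

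Both links can therefore be significant when the product of the estimates is only about a tenth of the target effect.

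**Can the separate tests tell mediation from none?** In 4000 simulated trials (75 per arm, total effect 4 points, assumed arm effect on the mediator 0.5 SD):
- True indirect effect 0.5 × 2.5 = 1.25 points (31% of 4): links 1 and 3 significant in 87% and 99% of trials.
- True indirect effect 0, with the mediator-outcome association due to confounding only: 86% and 99%.

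**Confounding by early recovery.** In 3000 simulated trials per setting, the PCS SD and correlations were those above and the true mediated effect was zero. Assumptions: arm effect on 8-week steps 0.5 SD; 8-week function correlated 0.65 with later function; standardised coefficient of 8-week function on steps 0.3, 0.4 or 0.5. For the last two rows, baseline steps also had an assumed coefficient of 0.5 on 8-week steps.

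| Analysis | 0.3 | 0.4 | 0.5 |
|---|---|---|---|
| Both links significant, arm omitted from link 3 | 67% | 79% | 85% |
| Both links significant, arm included in link 3 | 44% | 65% | 79% |
| Indirect-effect 95% CI excludes zero; arm, baseline function and baseline steps adjusted | 58% | 82% | 93% |
| As the row above, plus 8-week function | about 5% | about 5% | about 5% |

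The interval in the last two rows is a Monte Carlo product-of-coefficients interval. In the third row, testing the two links jointly in the same equations gives practically the same rates as the interval. The mean spurious indirect effect there was 0.9 to 1.6 points (0.9/4 = 22.5% to 1.6/4 = 40% of the target). Repeat runs moved the first two rows by a few percentage points.

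**The step measure.** If steps/hour is a 24-hour average, it equals steps/day ÷ 24. Every test is then unchanged, and only a product of coefficients taken without conversion would go wrong. For example, an assumed 1000 steps/day and 1.0 PCS point per 1000 steps/day give 1.0 point in matched units and 1.0/24 = 0.042 if unconverted. If steps/hour means per hour worn or active, it is a different variable.

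**The case against.** The strongest case against is that this is a condensed article, that an estimator for a secondary aim is commonly left to the statistical analysis plan, and that the narrower hypothesis is itself worded as association: "in turn, increased self-efficacy will be associated with higher levels of home exercise and physical activity at 8 weeks and 6 and 12 month" after surgery. The Analysis Plan tests that association. This stands in part. The text does not exclude an indirect-effect analysis elsewhere, and the narrower hypothesis is met. But the article writes out the sequence of link tests itself, and that sequence cannot answer the broader mechanism aim.

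Stronger readings are tempting but not supported:

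- A reader might infer that the links share no variable. Daily repetitions appear both as an outcome of the intervention and as a predictor of function, and self-efficacy is used consistently; only the step measure differs.
- A reader might infer that the step mismatch is why no mediated effect is estimated. The two are independent. The Exercise and Activity section also describes a summary per 24-hour period, which makes a pure unit slip plausible.
- A reader might infer that the trial intends to declare its mechanism confirmed from significant links. No passage says so.
- A reader might infer that adding an indirect effect is enough. The third row of the table shows otherwise: without 8-week function, the interval often excludes zero for the wrong reason.

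**Conclusion.** The concern holds in limited form. The mechanism aim is analysed by separate associations, which neither size a mediated effect nor distinguish one from confounding by early recovery. Under the assumptions stated, both links are significant in about 58% to 93% of trials with zero mediation when arm and baseline values are adjusted for, and in 44% to 85% in the simpler link models. These rates rest on an assumed 0.5 SD arm effect on steps and assumed step-function coefficients of 0.3 to 0.5; the documents give neither. No upper limit for the mediated share can be derived from the documents. The steps/hour and steps/day discrepancy is real but secondary, and may be one of units only. The primary PCS comparison and its power are untouched.

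**What to change.** In the Analysis Plan:

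- Use mean steps/day, as defined under Exercise and Activity, on both links.
- Put arm, baseline function and the baseline value of the mediator in every equation. Baseline self-efficacy, step monitoring and exercise logs are already collected.
- Estimate the indirect effect through 8-week activity on 6- and 12-month PCS with a bootstrap 95% CI, and keep the separate links as supporting results.
- Report that estimate both without and with adjustment for 8-week function. The Study assessments section schedules data collection at 8 weeks but does not itemise the instruments, so confirm that function is measured then.
- State the assumption of no unmeasured mediator-outcome confounding, or else word the mechanism conclusion as association only.

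The cost is modest extra analysis, with no new data if function is recorded at 8 weeks. Intervals will be wide with 150 completers. Adjusting for 8-week function may also remove some genuine early effect of the intervention, which is why both versions should be shown.
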